### 1) Instructions

Instructions in each of the modules are provided using animated drawings, i.e. 2D animations with a voice-over. The animation underlines the core elements of the therapy.

### 2) Case examples

The animations contain returning characters who have suffered from aviophobia (Bruno and Chloe) or arachnophobia (Michelle) and had overcome her/his specific phobia. Over the course of the modules this character describes how his/her phobia emerged and developed, what the consequences were for him/her and how s/he overcame it, i.e. through exposure therapy. These characters also provide user feedback and motivate the user to continue with his/her therapy program.

### **3) Virtual reality**

Aviophobia: the prototype immersive VR environment consists of a several flying situations:

- check in and luggage drop-off at the airport
- entering the gateway to the airplane
- take-off
- flying (during day- and night time)
- landing
- turbulence and storm

Arachnophobia: the prototype immersive VR environment consists of a several situations using augmented reality in which different types of spiders (e.g., small, large, thick or thin legs, hairy legs) are projected in the natural environment of the participant, e.g. on a table or on the arm of the participant.

### **4) Ecological momentary assessment**

Participants will be asked about their fear levels before, during and after the exposure VR: *How high is your fear at this moment? Please rate from 0 (no fear) to 10 (very high fear).*

#### **5.2 Use of co-intervention (if applicable)**

This study will not interfere with care-as-usual. ZeroPhobia is offered to the participants and can be followed in addition to care as usual if needed.

#### **5.3 Escape medication (if applicable)**

Not applicable.

## 6. INVESTIGATIONAL PRODUCT

### 6.1 Name and description of investigational product(s)

The ZeroPhobia application is a VR exposure-based intervention for smartphones and consists of six modules, each taking for about 5-20 minutes to complete. The objective of the intervention is to reduce subjects fear of flying or fear of spider symptoms through VR exposure using rudimentary, cardboard VR glasses. At the end of each level, the participant can increase, decrease, or keep the difficulty of the VR environment the same, in such a way that VR exposure is taxed optimally (e.g. not too difficult so that anxiety levels will not raise too high and not too easy so that anxiety levels are too low for exposure to be effective).

### 6.2 Summary of findings from non-clinical studies

Not applicable. No non-clinical studies have been conducted regarding ZeroPhobia.

### 6.3 Summary of findings from clinical studies

The working mechanism behind exposure therapy is based on Pavlov's learning theory of classical condition (Pavlov, 1927; Rescorla & Wagner, 1972). Numerous recent studies show that exposure therapy, virtual reality exposure therapy (VRET) and mobile app-based therapies are effective in reducing symptoms of anxiety.

- 1) (Meta-analytic) Studies of exposure therapy have repeatedly demonstrated to reduce anxiety levels of specific phobias in different settings (e.g. Kaczurkin & Foa, 2015; Wolitzky-Taylor et al., 2008). Exposure therapy is one of the most effective treatments (Wolitzky-Taylor et al., 2008).
- 2) VRET has shown to reduce anxiety and depression levels of participants with specific phobias with similar effectiveness compared to traditional, in-vivo exposure therapy (Goncalves et al., 2012; Krijn et al., 2004; Morina et al., 2015; Opris et al., 2012; Parsons and Rizzo 2008; Powers and Emmelkamp 2008; Raghav et al., 2016; Slater et al., 2006, 2013). Self-help VRET has also shown positive results (e.g. Piercey et al. 2012).
- 3) Recent research has demonstrated efficacy of mobile app-based therapies for anxiety and depression (Bakker et al., 2016; Donker et al., 2013). Research into mobile apps

as a method to intervene for psychiatric disorders are promising (e.g. Eysenbach et al., 2011; Saeb et al., 2015).

- 4) Recently we have demonstrated large effect sizes ( $d = 1.14$ ) when ZeroPhobia fear of heights was compared to a waitlist control group (Donker et al., 2019).

The above studies demonstrate the extensive research that has been done on exposure therapy and VRET in particular. The application of exposure therapy as an effective treatment of specific phobia indicates that there is no risk involved in offering VRET as an intervention and that the burden to participants is limited.

#### **6.4 Summary of known and potential risks and benefits**

The risks associated with offering ZeroPhobia to individuals who have symptoms of aviophobia or arachnophobia is minimal. In the undue case, participants may experience elevated distress, cyber sickness or fall (see section 13 for a more detailed description regarding the risks). Potential benefits of following ZeroPhobia are a decrease in anxiety symptoms.

#### **6.5 Description and justification of route of administration and dosage**

Not applicable.

#### **6.6 Dosages, dosage modifications and method of administration**

Not applicable.

#### **6.7 Preparation and labelling of Investigational Medicinal Product**

Not applicable.

#### **6.8 Drug accountability**

Not applicable.

### **7. NON-INVESTIGATIONAL PRODUCT**

#### **7.1 Name and description of non-investigational product(s)**

Not applicable.

## **7.2 Summary of findings from non-clinical studies**

Not applicable.

## **7.3 Summary of findings from clinical studies**

Not applicable.

## **7.4 Summary of known and potential risks and benefits**

Not applicable.

## **7.5 Description and justification of route of administration and dosage**

Not applicable.

## **7.6 Dosages, dosage modifications and method of administration**

Not applicable.

## **7.7 Preparation and labelling of Non Investigational Medicinal Product**

Not applicable.

## **7.8 Drug accountability**

Not applicable.

#### **8.1.2 Secondary study parameters/endpoints (if applicable)**

- Aviophobia: The self-report Flight Anxiety Modality questionnaire (FAM; van Gerwen et al., 1999) has 18 items measuring anxiety and anticipation anxiety symptoms in flight situations. The FAM has a 5-point Likert answering scale type, from 1 (completely not) to 5 (very intense). The reliability is good (Nousi et al., 2008).
- Questions related to aviophobia: duration of the problem, amount of flights undertaken, safety behaviours, presence of negative flight experiences (at baseline) and questions about whether participants have taken a flight after ZeroPhobia (post-test, follow-up)
- Arachnophobia: The Spider Phobia Questionnaire (Klorman, Hastings, Weerts, Mela-med, & Lang, 1974), a 31-item self-report questionnaire for measuring spider anxiety. This questionnaire is often used for research into spider fear. The SPQ has been found to be high in internal consistency (Johnsen & Hugdahl, 1990).
- Beck Anxiety Inventory (BAI; Beck et al., 1988) is a 21-item self-report questionnaire assessing symptoms of anxiety. Patients record how much they have been bothered by each symptom during the past week, including the day the questionnaire is administered. Each item is rated on a 4-point Likert scale ranging from 0 = not at all to 3 = severely: I could barely stand it. The total score ranges from 0 to 63. The following guidelines are recommended for the interpretation of scores: 0 – 9, normal or no

anxiety; 10 – 18, mild to moderate anxiety; 19 – 29, moderate to severe anxiety; and 30 – 63, severe anxiety. Internal consistency is high (0.90 – 0.94) and convergent validity is good (Brown et al., 1997).

- The nine-item mood module of the Patient Health Questionnaire (PHQ-9; Kroenke et al, 2007) is used to screen subjects with depressive disorders. The 9 items are each scored 0 – 3, total score range is 0 – 27. In a review of Wittkamp et al. (Wittkamp et al., 2007), a sensitivity of 0.77 (0.71 – 0.84) and a specificity of 0.94 (0.90 – 0.97) was found for the PHQ-9. This questionnaire will be completed at baseline, post-test and follow-up.
- The Web Screening Questionnaire (WSQ; Donker, [name], Marks, and Cuijpers, 2009) is a 15-item questionnaire aimed to screen for depressive disorder, alcohol abuse/dependence, GAD, PTSD, social phobia, panic disorder, agoraphobia, specific phobia, and OCD. Only three items of the WSQ will be asked for the purposes of this study – panic disorder, agoraphobia, and OCD. The questionnaire has been found to have both good sensitivity (0.72 – 1.00) and specificity (0.44 – 0.77) (Donker et al., 2009).
- The Interpersonal Reactivity Index (IRI; Davis, 1980) is a self-report questionnaire measuring different types of empathy. 7 items from the sub-section 'Fantasy' will be given to participants as baseline. This will be used to measure general ability to fantasize and experience absorption or transportation into fantasy worlds. This questionnaire has been found to be reliable and valid (Davis, 1994).

### **8.1.3 Other study parameters (if applicable)**

- Demographic variables (gender, age, education level, marital status, employment status).
- System Usability Scale (SUS; Bangor et al., 2008): 10 items about user friendliness of the app. The SUS is composed of 10 statements that are scored on a 5-point scale of strength of agreement. Final scores for the SUS can range from 0 to 100, where higher scores indicate better usability. This means that products that are at least passable have SUS scores above 70, with better products scoring in the high 70s to upper 80s. Truly superior products score better than 90. Products with scores less than 70 should be considered candidates for increased scrutiny and continued improvement and should be judged to be marginal at best. Reliability is good (Bangor et al. 2008). This questionnaire will be completed at post-test.
- User-friendliness of ZeroPhobia as a treatment will be in part measured with the 6-item self-report treatment expectation and satisfaction scale called the

Credibility/Expectancy Questionnaire (CEQ; Devilly & Borkovec, 2000). The CEQ measures expectations of the participants before the start of the treatment. This questionnaire will be used alongside the post-test SUS and NEQ to determine if ZeroPhobia did in fact meet expectations.

- User-friendliness will also be measured using single item questions directly asking about the user experience of ZeroPhobia and the realism of the VR environments. This also includes one open question asking for any other feedback on the app a participant would like to give.
- Igroup Presence Questionnaire (IPQ; Schubert, Friedmann and Regenbrecht 2001), a 14-item questionnaire, which assess realism and “presence” in the VR environment. Each of the items has five response categories from fully disagree (1) to fully agree (5). Chronbach`s alpha is good ( $\alpha = .73$ ). This questionnaire along with some open questions about user experience of the VR environment will be completed at post-test.
- Ecological Momentary Assessment: One question about current anxiety level during exposure in VR
- Usage data from the ZeroPhobia app: frequency and duration of practice during exposure in VR, frequency and duration of time spent in the modules.
- Flight usage questions, including when was the last time you flew on an airplane, how many times have you flown in the past 3/12 months and how long was each of these flights?
- Professional treatment (medication and other psychiatric treatment) will be asked during the screening process, but also at post-test and follow up timepoints in order to control for possible other therapeutic effects.
- Negative Effects Questionnaire (NEQ; Rozental et al., 2016) consists of 32 questions and will be used to assess side effects of psychological treatments. Each question can be answered either ‘yes’ or ‘no.’ If yes, participants are then asked to rate how negative the experience of this item was on a 5-point Likert scale (from ‘not at all’ to ‘extremely’). Participants are then asked to determine whether this experience was probably caused by ‘the treatment that I am undergoing’ or ‘other circumstances.’ The NEQ has been found to have good validity (Rozental et al., 2019).

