## **3. STUDY DESIGN**

A randomized controlled design will be carried out, in which the effectiveness and user-friendliness of an online app-based VR self-help treatment 'ZeroPhobia: Aviophobia' and 'ZeroPhobia: Arachnophobia' will be evaluated. In this study, 96 (aviophobia) and 72 (arachnophobia) participants from the Dutch general population will be randomized in 2 separate RCTs over 2 conditions: the experimental condition (ZeroPhobia: Aviophobia or Arachnophobia) and a waitlist control condition. The duration of the intervention will be 6 weeks. Measures will be taken at baseline, directly after the intervention (6 weeks) and at 3- and 12- month follow-ups. All measures will be completed online. Subjects in the wait-list condition will receive the intervention after completion of the post-test. Randomization (block randomization with 6, 8, 10, and 12 blocks) will be performed by an independent researcher. Figure 1 presents the flow chart of the study.

[figure not shown]

Figure 1: flow chart

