## 8.2 Randomisation, blinding and treatment allocation

The allocation scheme will be created by an independent researcher with a computerized random number generator (Random Allocation Software) with block sizes of 6, 8, 10, and 12 and at an allocation ratio 1:1. Participants will be randomized into two groups: ZeroPhobia or

waitlist condition. Due to the nature of the study, double blinding for treatment allocation is not possible.

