If in the intervention condition, the research assistant will send the VR glasses to the participant by postal delivery, along with usage instructions. The research assistant will email the participant with instructions on how to download the ZeroPhobia app to his/her smartphone. The app is locked with an individual code which will be given to the participant at the start of the intervention. Participants can then begin the ZeroPhobia intervention which they can follow for 6 weeks (5-20 minutes per week, in addition to VRET from module/week 3 onward, which we recommend 10 minutes a day of practice with). When practicing in VRET, participants are asked to fill in one question about their anxiety level before, during, and after VRET (duration: 5 seconds). Participants can follow the intervention at their own pace. Participants will receive weekly automatic reminder emails to begin or continue the intervention from the research assistant. If needed (e.g., with a question about how to use ZeroPhobia or in the unlikely case of distress), participants will be invited to contact the research assistant.

If in the wait-list condition, the participant will be informed that after a six week pause and the completion of a post-test assessment, they can begin the ZeroPhobia program. The wait-list group will undergo the same program procedure as those in the treatment condition. Participants of both conditions will begin the program on the first working Monday after

completing the baseline and being randomized to a condition, meaning participants of both groups will have different start and end times. Both groups will have the same duration of each section, however (see flowchart).

The aforementioned post-test (occurring after 6 weeks of either intervention or pause, or after the completion of module six in the intervention group (for those participants who choose to work through the ZeroPhobia program faster) consists of the FAS and FAM (aviophobia) or FSQ and SPQ, (arachnophobia), PHQ, BAI, IPQ, SUS, CEQ and NEQ, questions regarding whether they received professional treatment during this time, and questions about flight usage (duration: 25 minutes). Two reminders will be given across two weeks to fill in post-test, the first being an e-mail and the second a phone call.

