| CEQ                                               | To determine program's user-friendliness                                            | x |   |   |
| NEQ                                               | To determine whether there are any negative effects of ZeroPhobia                   |   | x |   |
| IPQ                                               | VR experience                                                                       |   | x |   |
| IRI                                               | To determine influence of fantasizing ability on effectiveness of VRET              | x |   |   |
| WSQ                                               | To control for confounding variables                                                | x |   |   |
| Flight usage                                      | To determine effectiveness of treatment                                             | x | x | x |
| General flight anxiety questions                  | To further understand the type of flight anxiety a participant has                  | x |   |   |
| User-friendliness and realism questions           | To further understand the user experience of the ZeroPhobia app and VR environments |   | x |   |
| Professional treatment (medication and treatment) | To control for confounding variables                                                | x | x | x |

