### **8.6 Follow-up of subjects withdrawn from treatment**

If a subject is withdrawn from treatment, either due to their own decision or the decision of the research staff, they will still be followed-up with. All participants will be included in the intention-to-treat (ITT)-analyses.

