If after completion of ZeroPhobia: Fear of Flying participants still have questions about their aviophobia or wish for further treatment, then we will encourage them to contact 'Stichting VALK.' Stichting VALK is an anxiety treatment institute that was created in 1990 in cooperation with University of Leiden, KLM, and Schiphol Airport ([www.valk.org](http://www.valk.org); [[contact]](mailto:[contact])).

Participants will not be withheld regular care during the study; a participant who wishes to seek additional help for their phobia or any other medical issues will not be prevented from doing so.

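### Outside treatment reported at post-test is labelled a variable to control for, but it arises after randomisation and should not be adjusted for in the app-versus-waitlist comparison

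*Protocol*

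**What the plan says.** Section 8.1.3 states that medication and other psychiatric treatment are asked about at screening, but "also at post-test and follow up timepoints in order to control for possible other therapeutic effects". Table 1 (section 8.3) lists professional treatment with the aim "To control for confounding variables" and marks it at baseline, post-test and follow-up. The other row with that aim, the WSQ, is marked at baseline only.

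The post-test assessment in section 8.3 includes "questions regarding whether they received professional treatment during this time", meaning the six weeks of app use or waiting.

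Outside care is allowed. Section 5.2 says "ZeroPhobia is offered to the participants and can be followed in addition to care as usual if needed", and section 11.3 says "a participant who wishes to seek additional help for their phobia or any other medical issues will not be prevented from doing so". Participants are told their condition, and section 8.2 notes that "double blinding for treatment allocation is not possible". On the comparator, section 3 says "Subjects in the wait-list condition will receive the intervention after completion of the post-test".

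For the analysis, section 8.6 says "All participants will be included in the intention-to-treat (ITT)-analyses". Section 10.1 names repeated measures ANOVA for intention-to-treat and independent-sample t-tests for per protocol. It lists no covariates, and says the choice of procedure will be reviewed before the data are analysed.

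**The concern.** In a randomised comparison a confounder must precede allocation. Treatment status at screening or baseline meets that test. Treatment taken up during the six randomised weeks does not. A waitlist participant knows that nothing is on offer yet and may have more reason to look elsewhere, and someone whose fear has not eased may be more inclined to do so. The post-test answer can therefore be partly a consequence of allocation and partly a marker of the outcome.

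Entering it as a covariate would compare arms within levels of something the arm may have changed. That estimates neither the intention-to-treat effect nor, in general, the effect that would be seen if nobody used outside care. At stake is the post-test FAS or FSQ contrast, which is the primary between-group comparison in both trials.

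**Working it through.** **The plan's own figures.** Section 4.3 uses d = 0.70 (aviophobia) and d = 0.80 (arachnophobia), two-sided alpha 0.05, power 0.80, 1:1. The t-based sample size is 33.02, so 34 per arm, and 25.52, so 26 per arm. Both stated figures reproduce, and this point changes neither. The yardstick below is d = 0.70. With 34 evaluable per arm its standard error is about √(2/34) = 0.24 SD.

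**Formula.** Write effects as reductions in fear in SD units. Let p_w and p_a be the uptake of outside care in the waitlist and app arms, and γ the coefficient of the uptake indicator in the adjusted model (positive if users of outside care score more fearful at post-test, other terms held fixed). In large samples:

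adjusted effect − ITT effect = −γ × (p_w − p_a)

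The shift is zero if uptake is equal by arm or if γ = 0. Its sign follows γ when the waitlist uses more care.

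**Inputs.** The protocol gives neither uptake rates nor an effect of outside care. Everything below is assumed. Results were checked by large-sample simulation.

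1. *Outside care helps by 0.5 SD; uptake unrelated to fear.* Then γ = −0.5. With uptake of 30.0% versus 5.5%, the shift is 0.5 × 0.245 = +0.12. ITT is 0.58 and the adjusted value 0.70. Over waitlist uptake of 5% to 30%, with lower uptake in the app arm, the shift was +0.02 to +0.12.

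2. *Outside care has no effect; uptake rises with post-test fear; baseline in the model (correlation 0.7 with post-test).* The simulated adjusted effect at 20% versus 5% is 0.59, so γ is about 0.11/0.15 = 0.7. Using γ = 0.7:

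| Uptake, waitlist vs app | Shift | Adjusted effect (ITT 0.70) |
|---|---|---|
| 10% vs 10% | 0 | 0.70 |
| 10% vs 5% | −0.7 × 0.05 = −0.035 | about 0.66–0.67 |
| 20% vs 5% | −0.7 × 0.15 = −0.105 | about 0.59 |
| 30% vs 5% | −0.7 × 0.25 = −0.175 | about 0.52–0.53 |

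Halving the link between fear and uptake gives 0.68, 0.64 and 0.60 in the last three rows. Without baseline in the model, 20% versus 5% gives 0.51, a shift of −0.19.

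3. *Outside care has no effect; uptake depends only on baseline fear, and baseline is in the model.* Then γ = 0 and the adjusted effect is 0.70 at every uptake level.

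4. *Uptake depends on an unmeasured severity factor and outside care helps by 0.5 SD.* The two shifts nearly cancel: 0.58 ITT against 0.58 adjusted at uptake of 33% versus 8%.

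5. *As in 2, at 20% versus 5%, but outside care helps by 0.5 SD.* ITT is 0.70 − 0.5 × 0.15 = 0.62 and the adjusted value is 0.59. The adjusted value equals neither the ITT effect nor the 0.70 that would apply without outside care.

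**The case against.** The strongest reply is that no planned analysis uses the variable. The two phrases explain why an item is collected; they sit in a measures list and in a table column of aims. Sections 10.1 to 10.3 never mention professional treatment, and covariate lists are commonly left to the statistical analysis plan. This stands. A reader might infer that the primary analysis is already conditioned on outside care and therefore biased, and the protocol does not support that. What remains is that it gives adjustment as the purpose in two places, promises intention-to-treat elsewhere, and leaves the final procedure open. An analyst who adjusted could cite the protocol for it.

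A second reply is that controlling for other treatment makes sense at follow-up. This also stands. Section 8.3 sends the 3- and 12-month questionnaires to the intervention arm only, and section 2 defines sustained effect as change from baseline within that arm. With no control group, outside treatment over a year is a genuine rival explanation. A reader might infer that only the baseline value is ever useful, but that goes too far.

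A third reply is that uptake is probably low. The exclusion criteria remove people in current treatment, unless on a stable dosage with no planned change. The window is six weeks, the waitlist then gets the app, and section 1 describes poor access to care. This makes the smaller scenarios more plausible, but nothing rules out uptake that differs by arm.

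Finally, the larger downward shifts come from letting uptake depend on the post-test score itself, although the care began before that score was taken. This is fair, and the results change with that choice. A reader might infer that adjustment would always understate the app's effect; scenario 1 goes the other way.

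**Conclusion.** The point holds as a conditional one. The stated purpose is wrong for the post-test between-group comparison: treatment received after randomisation is not a confounder there, and adjusting for it would depart from the intention-to-treat effect that sections 8.6 and 10.1 promise. The ANOVA and t-tests as written are unadjusted, so harm arises only if the stated purpose is carried out as covariate adjustment.

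Neither size nor direction can be established from the protocol. Across the assumed scenarios the shift ran from zero to +0.12 SD and to −0.19 SD, and was about 0.03 SD at 10% versus 5%. These are illustrations and not bounds. Against a standard error of about 0.24 SD, the low-uptake case is minor. The larger cases are roughly half to four-fifths of a standard error (0.12/0.24 and 0.19/0.24). The correction is worth making because it costs almost nothing and resolves an inconsistency on the primary contrast.

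**What to change.** In section 8.1.3 and the professional-treatment row of Table 1:

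- Limit adjustment of the post-test between-group comparison to treatment status at screening/baseline.
- State that treatment started or changed after randomisation is reported by arm and is not a covariate in the primary or secondary between-group models.
- State that the intention-to-treat comparison holds regardless of outside care, with any other handling only as a labelled sensitivity analysis.
- For the within-arm 3- and 12-month change, say that outside treatment will be described and may be examined as an alternative explanation.

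The item should still be collected at all time points; only its stated use changes. The cost is a few sentences of protocol wording, with no new data, assessments or participants.
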